### Follow-up

Both the intervention and control group will follow the same protocol for monitoring the curvature during the two years of the study. Every four months the orthopedic surgeons will repeat the measurements of size and location of the abnormal curvature, physical height, maturation characteristics (menarche and Risser sign), brace compliance, and whether or not surgery is indicated. These examinations will be conducted following a specific protocol: every four months a physical examination and an X-ray of the spine will take place. Patients will take off the brace the night before an X-ray is taken. Standard technique is a standing position of the patient and a posteroanterior projection. In patients with discrepancy in leg length, boards will be put under the shortest leg to correct for this.

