### Sample size

The Cobb angle at inclusion will on average be 29 degrees (range 22–35 degrees). Due to the standard error of radiographic production and intra and inter-observer measurement variation, a measurement error in Cobb angles of 5 degrees will appear [1]. To reduce the standard error of radiographic production, all patients will undergo X-ray following a strict protocol. Because inter-observer measurements errors are reduced (see *Outcomes*), measurement error will than be maximal 2 degrees, thus the 95% observation interval of Cobb angles at inclusion is 20–37 degrees. After two years, when the outcome will be determined, the range in change will be 0–15 ± 2 degrees. Assuming a uniform distribution of this change in Cobb angle between the patients after two years (most unfavorable scenario), the standard deviation of the difference in change between baseline and outcome measurement will be about 4.5 degrees.

Since bracing has to be better than observation to be justified as treatment for IS, a superiority design will be used. With a power of 95% and alpha = 0.05, a mean difference of 5 degrees between the groups can be detected with 40 patients in both study arms. We will aim at a study population at start of 100 patients to take loss to follow-up into account.

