### Statistical methods

The intervention and control group will be compared based on the 'intention to treat' principle. Differences in Cobb angle between the two groups and other continuous parameters will be measured using parametric or non-parametric tests (depending on skewness) for group comparisons. Categorical parameters will be compared by the Chi-square test. Logistic regression will be applied to measure the treatment effect (yes/no progression) adjusting for covariates. Since we have 4-month measurements on Cobb angles in both arms, progression in Cobb angle will be analyzed with a linear mixed effect model, where we will assume a simple compound symmetry structure. This may be particularly important for extrapolations to follow-up periods longer than 2 years after entry.

When a patient in the control group had to be braced before the end of the follow-up (because of a more than 10 degree progression of the curvature), her/his Cobb angle at the moment of commencing treatment will be considered as final outcome and will be included in the analysis.

In a second analysis, we will perform Kaplan-Meier analyses with these 'progression to more than 10 degrees' as events, in both arms (intention-to-treat).

Stratified analysis will be done to evaluate whether curve type, brace compliance, Cobb angle at inclusion and Risser sign at inclusion influence the effectiveness of brace treatment. Using logistic regression we will also evaluate whether brace compliance depends on gender and age.

Health-related quality of life and utilities will be compared between the intervention and control group. This will be done by basic descriptive statistics. Depending on the distribution of the data, parametric or non-parametric tests will be used.

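### Compound symmetry does not fit curves that fan out, so the mixed model's inference on progression over time, and any extrapolation from it, would look too precise

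*Protocol article*

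**What the plan says.** The Statistical methods section of the protocol article says that "progression in Cobb angle will be analyzed with a linear mixed effect model, where we will assume a simple compound symmetry structure". It adds: "This may be particularly important for extrapolations to follow-up periods longer than 2 years after entry". The data come from a fixed schedule (Follow-up): "every four months a physical examination and an X-ray of the spine will take place". Over two years that is 7 time points, counting baseline.

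The Sample size section describes how patients are expected to differ: "the range in change will be 0–15 ± 2 degrees", with "Assuming a uniform distribution of this change in Cobb angle between the patients after two years", a case that the article calls the least favourable one. It also says that "measurement error will than be maximal 2 degrees" and that "the standard deviation of the difference in change between baseline and outcome measurement will be about 4.5 degrees".

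Statistical methods also plans ordinary two-group tests, parametric or not. The article does not say which analysis decides the primary question, although Outcomes calls bracing potentially effective only if mean two-year progression differs by 5 degrees or more in its favour.

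**The concern.** Under compound symmetry, patients differ by a constant shift and otherwise follow their group's mean course. The Sample size section assumes that some patients progress by nothing and others by 15 degrees, and that little of this spread is reading error. Variance then grows over follow-up, and the correlation between two visits falls as they lie further apart. The model has no place for this, so it counts real differences in progression as independent noise at each visit. Seven visits then seem to carry far more information about the difference in progression than they do.

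At stake are the confidence interval and p-value for the difference in progression rate, and the width of any interval projected past month 24. The covariance structure is written into the article, so this is not a detail left to a fuller analysis plan.

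**Working it through.** **Inputs.** From the article: 7 visits; change uniform over 0 to 15 degrees; measurement error at most 2 degrees; SD of change about 4.5; 40 per arm. Assumed here: individual progression is roughly linear, compound symmetry means a random intercept with model-based standard errors, and tests are two-sided at 5%. The 2-degree limit is read in two ways: as a 95% limit (reading SD *s* about 1) or as an SD (*s* = 2).

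**The article's SD.** The between-patient variance of change is B = 15²/12 = 18.75 (SD 4.33). Adding reading error at both ends, √(18.75 + 2×1²) = 4.56, close to the stated 4.5. With *s* = 2 the same sum gives √26.75 = 5.17. To keep a total SD of 4.5 with *s* = 2, B must fall to 4.5² − 2×2² = 12.25.

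**Formulas.** Scale time so that two years = 1. The sum of squares of the visit times is S = 28/36 = 0.778.
- True variance of one patient's fitted slope: B + s²/S.
- Residual variance under compound symmetry: w = (B·S + 6s²)/6. The model's slope variance is w/S.
- Month-24-minus-baseline contrast with visit as a category: true variance B + 2s², model variance 2w.
- SE ratio r = √(true/model). Type I error = P(|Z| > 1.96/r). Arm size cancels.

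**Worked case, B = 18.75, s = 1.**
- Slope: true 18.75 + 1/0.778 = 20.04. w = (14.58 + 6)/6 = 3.43, so the model gives 4.41. r = √(20.04/4.41) = 2.13; type I error 0.36.
- Month-24 contrast: r = √(20.75/6.86) = 1.74; type I error 0.26.

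| B | s | slope: true / model | r | type I | month 24: true / model | r | type I |
|---|---|---|---|---|---|---|---|
| 18.75 | 1 | 20.04 / 4.41 | 2.13 | 0.36 | 20.75 / 6.86 | 1.74 | 0.26 |
| 18.75 | 2 | 23.89 / 8.27 | 1.70 | 0.25 | 26.75 / 12.86 | 1.44 | 0.17 |
| 12.25 | 2 | 17.39 / 7.19 | 1.56 | 0.21 | 20.25 / 11.18 | 1.35 | 0.15 |

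In degrees, for the first row with 40 per arm, the SE of the two-year slope difference is √(20.04×2/40) = 1.00, but the model reports √(4.41×2/40) = 0.47.

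**Simulation under no effect** (4,000 trials per setting, 40 per arm, rows in the same order):
- Compound-symmetry slope: 0.372, 0.248, 0.215.
- Compound-symmetry month-24 contrast: 0.271, 0.166, 0.152.
- Test on per-patient slopes, which allows slopes to vary: 0.053, 0.044, 0.052.
- Two-group t-test of two-year change: 0.052, 0.043, 0.052.
- Average effect over all visits: 0.052, 0.051, 0.048.

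A fitted mixed model (150 trials, B = 18.75, s = 2) rejected in 21% with a random intercept only (mean SE 0.32 degrees per year) and in 4% with a random slope (mean SE 0.55).

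**Where it vanishes.** The rate returns to 5% only if all change is reading error, s = 4.5/√2 = 3.2, above the article's stated maximum of 2.

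**Extrapolation.** If time enters linearly, the projected change over a horizon is the slope times that horizon. Its SE is understated by the same factor r, and the shortfall in degrees grows with the horizon.

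**The case against.** A reader might infer that an ineffective brace could easily be declared effective. The article does not support that. The covariance choice alters the standard error and, in balanced data, leaves the estimated difference unchanged, while Outcomes asks for a difference of 5 degrees. With no effect, SD 4.5 and 40 per arm, the SE is 4.5×√(2/40) = 1.01, so z = 5/1.01, about 5. The chance of meeting the rule is roughly 3 in 10 million. Even with B = 18.75 and a reading SD of 2.5, above the stated maximum, the SE is √(31.25×2/40) = 1.25, z = 4, and the chance is about 3 in 100,000. This part of the objection stands.

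A reader might also infer that every efficacy test is invalid. That does not follow either: the plain comparison of two-year change and the average effect over visits hold their size.

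The treatment-by-time term is not named, nor is it said whether time is linear or categorical. That is true, but a treatment contrast over time is the natural result of a model of progression, and both forms are affected. For the same reason, it cannot be said that the plan projects a straight line past the end of growth.

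The 36% is the top of the range. It reads 2 degrees as a 95% limit and uses the spread that the article calls least favourable. This also stands, and a range is given for that reason. Only the ratio of between-patient to reading variance matters: halving the spread at *s* = 1 gives the same 25% as the second row of the table.

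Finally, Statistical methods fixes a control patient's outcome when bracing starts after more than 10 degrees of progression. Carrying values forward after such progression in both arms still gives 0.23 to 0.33 for the slope. Doing so in controls only gives 0.25 to 0.38, but there the plain t-test also rises, to 0.06 to 0.07, so part of that excess comes from the carry-forward and not from the covariance.

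**Conclusion.** The point holds within limits. The stated covariance structure conflicts with the article's own picture of how patients differ. For a treatment-by-time slope, the SE is understated about 1.6- to 2.1-fold and two-sided type I error is about 21% to 36%. For a month-24-minus-baseline contrast from the same model it is about 15% to 26%. Extrapolation intervals are too narrow as well.

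These sizes rest on roughly linear individual progression, model-based standard errors, the article's spread of change, and a reading SD between 1 and 2. The direction holds for any pattern in which curves fan out. The fault lies in the mixed model's inference on progression and in extrapolation from it, and does not reach the plain two-year comparison.

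**What to change.** Replace compound symmetry in Statistical methods with an unstructured covariance over the 7 visits, or with a random intercept plus random slope. Report the month-24 difference between arms from that model. Do not base extrapolation beyond two years on the compound-symmetry model. An unstructured model with visit as a category says nothing past month 24, so any projection needs its own stated model.

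The change takes about one sentence. Compound symmetry has 2 covariance parameters. A correlated random intercept and slope with residual variance has 4, and an unstructured matrix has 7×8/2 = 28. With 80 to 100 patients and 7 visits (560 to 700 planned measurements) either can be estimated. The intervals become wider, which is the correct width.

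### Effect modification by curve type, baseline Cobb angle and Risser sign is to be evaluated by stratified analysis, but no test comparing the brace effect between strata is named

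*Protocol article*

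**What the plan says.** The Statistical methods section of the protocol article gives one sentence to effect modification of bracing: "Stratified analysis will be done to evaluate whether curve type, brace compliance, Cobb angle at inclusion and Risser sign at inclusion influence the effectiveness". It defines no strata or cut-points and does not say how results from different strata will be compared.

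The same section names several analyses of the treatment effect:
- For continuous outcomes, "parametric or non-parametric tests (depending on skewness) for group comparisons".
- For a binary version of the outcome, "Logistic regression will be applied to measure the treatment effect (yes/no progression) adjusting for covariates".
- For the four-monthly measurements, "progression in Cobb angle will be analyzed with a linear mixed effect model".
- Kaplan-Meier analysis of progression beyond 10 degrees, by arm.

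None of these is linked to the effect-modification question, and no treatment-by-factor term is mentioned. The Sample size section addresses only the overall comparison: "a mean difference of 5 degrees between the groups can be detected with 40 patients in both study arms".

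**The concern.** Asking whether a factor influences effectiveness sets up the null hypothesis that the brace effect is the same at every level of that factor. Comparing the arms inside one stratum has a different null: that there is no brace effect in that stratum. Two strata can share the same true effect and still fall on opposite sides of 0.05, because each is small and the smaller one has less power. A set of within-stratum results therefore needs a direct comparison of the effects before it says anything about modification, and the article does not name one.

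At stake is a secondary statement that bracing works for one curve type or Risser grade but not for another, when the data show no such difference. The article describes bracing as burdensome, so a spurious statement of that kind would not be harmless. The overall effectiveness conclusion does not depend on it.

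**Working it through.** **Inputs from the Sample size section.** Difference 5 degrees; SD of change 4.5 degrees; 40 per arm, with 100 enrolled (50 per arm if nobody is lost); power and alpha from "With a power of 95% and alpha = 0.05". I take alpha as two-sided. The Participants section admits Risser sign up to 2, so grades 0, 1 and 2 make three strata possible.

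**Assumptions.** The number and sizes of strata are not given. I use two equal strata, a 70/30 split and three equal strata. The rule tested, significant in one stratum and not in another, is also an assumption.

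**The plan's own figure.** n per arm = 2 × (1.960 + 1.645)² × 4.5² / 5² = 21.05, so 22 rather than the stated 40. An SD of about 6.2 would give 40. That mismatch is a separate point. It is used here only to show how the results move with a larger SD.

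**Power within strata, same 5-degree effect everywhere, SD 4.5** (non-central t, two-sided 0.05, n per arm in the stratum):
- n = 20: 0.928
- n = 28: 0.983
- n = 12: 0.739
- n = 13: 0.776
- n = 25 (50 per arm, two equal strata): 0.971

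**Chance that strata disagree on significance.** For two strata this is p₁(1 − p₂) + p₂(1 − p₁). For k equal strata it is 1 − pᵏ − (1 − p)ᵏ.
- Two equal strata: 2 × 0.928 × 0.072 = 0.13
- Two equal strata, 50 per arm: 2 × 0.971 × 0.029 = 0.06
- 70/30 split: 0.983 × 0.261 + 0.739 × 0.017 = 0.27
- Three equal strata: 1 − 0.776³ − 0.224³ = 0.52

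**Sensitivity.** With a common effect of 3.7 degrees at SD 4.5, or 5 degrees at SD 6.1, the three figures at 40 per arm become about 41%, 51% and 75%. The 3.7 degrees is close to what 40 per arm detects with 95% power: 3.605 × 4.5 × √(2/40) = 3.63 by the normal approximation.

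**Interaction test on the same data.** Under a uniform effect, the simulated rejection rate for two strata was 4.8% to 5.3% in the settings tried, including the 13% and 27% cases. With three and four strata, the interaction F test also stayed between about 4% and 6%.

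**Power of the interaction test.** With 20 per arm in each of two strata, the standard error of the difference between stratum effects is 4.5 × √(4/20) = 2.01 degrees. For a 5-degree difference in effect, 5 / 2.01 = 2.48. Power is 70% by the normal approximation and 69% by the t distribution. Reaching 80% needs a difference of about 5.6 degrees.

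**The case against.** The strongest reply is that the article does not prescribe the faulty rule. It says stratified analysis and stops there. It does not say that p-values will be computed within strata, or that a difference in significance will count as modification. Stratified analysis can mean estimates with confidence intervals and can include a homogeneity test, which an analysis plan not shown might specify. This stands in full as a limit on the percentages: they describe an inferred reading.

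A reader might also infer that the two-group test is the only comparison available. It is not, since logistic, mixed and Kaplan-Meier analyses are named as well. None is tied to effect modification, but the mixed model could carry the needed term.

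A reader might further infer that false subgroup findings would be frequent whatever the design of the strata. At the protocol's own effect and SD with one even split, the figure is 13%, or 6% if all 50 per arm are evaluable. The larger figures need uneven or three-level strata, a smaller effect or a larger SD.

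Nor do the documents show that subgroup results would go straight into advice on whom to brace. No research question concerns subgroups, and the effectiveness criterion is the overall mean difference.

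What does not stand is the view that this is only detail left to a fuller document. The article poses an effect-modification question and names a method for it, and that method does not by itself compare effects.

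**Conclusion.** The point holds in limited form. For curve type, Cobb angle and Risser sign at inclusion, the named method lacks the comparison between strata that the question requires. If strata were judged by their significance, a uniform effect would look like a subgroup difference in about 6% to 52% of trials at 5 degrees and SD 4.5, depending on the assumed strata and on whether 40 or 50 per arm are evaluable. An interaction test would do so in about 5%.

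The documents do not support saying that the plan, followed as written, produces these errors, because the comparison rule is not written. The analysis is secondary and exploratory.

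Brace compliance appears in the same sentence but is a separate problem. It arises after randomisation and has no counterpart in unbraced controls, so neither stratification nor a plain interaction term answers it.

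**What to change.** For the three baseline factors, replace the sentence with a rule of this kind: modification of the brace effect by curve type, Cobb angle at inclusion or Risser sign at inclusion will be judged by the treatment-by-factor interaction in a linear model of progression (or in the mixed model already planned) in all randomised patients. Cobb angle enters as a continuous term and Risser sign as an ordered term. Stratum-specific mean differences with 95% confidence intervals are shown as description only, and a difference in significance between strata is not taken as evidence that the effect differs. Compliance should be handled apart.

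The cost is a short change to the text and one interaction term per factor, with no new data or patients. A continuous Cobb term brings a linearity assumption. Because the interaction test has limited power, smaller differences in effect would often be missed and fewer subgroup claims would be possible.

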### Participants

Eligible patients are girls and boys in the age group 8–15 years whose diagnosis of IS has been established by an orthopedic surgeon, who have not yet been treated by bracing or surgery, and for whom further growth of physical height is still expected based on medical examination and maturation characteristics (Risser sign) established by X-ray. To expect further growth of physical height, only patients with a Risser sign ≤ 2 will be included. All participating orthopedic surgeons agreed that the Cobb angle of the eligible patient should either be minimally 22 and maximally 29 degrees with established progression of more than 5 degrees, or should be minimally 30 and maximally 35 degrees; established progression for the latter is not necessary. At inclusion of the study, data on calendar age, gender, height, maturation characteristics (Risser sign, menarche), size and location of the curvature will be recorded for all patients.

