### Control group

Patients in the control group will initially not be braced during the two study years, unless their curvature shows more than 10 degrees progression compared to the Cobb angle at inclusion. In this case, the orthopedic surgeon, patients and their parents could decide to start brace treatment. The patients in the control group are allowed to attend physical therapy if they want to, because physical therapy alone will not prevent further progression of the curvature.

In case patients of the control group reach Cobb angles that require surgery, they can be operated.

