The secondary outcomes of this study concern health-related quality of life (HRQoL) and compliance to brace treatment. Because bracing is a burdensome procedure (including reduced activity in daily living, pain, and implications for self-esteem, satisfaction with appearance, and mood), HRQoL will be evaluated in the intervention and control group by a generic HRQoL questionnaire, i.e. Child Health Questionnaire-Child Form 87 items (CHQ-CF87) and the Child Health Questionnaire-Parent Form 50-items, (CHQ-PF50) EuroQol including a VAS for general health, and a disease-specific questionnaire, i.e. the adjusted Scoliosis Research Society-22 Patient Questionnaire for Idiopathic Scoliosis (SRS-22r Patient Questionnaire). These questionnaires have been translated into Dutch; score distribution and internal consistency corresponded with the original versions [14-16]. Patients will be asked to fill out the CHQ-CF87, EuroQol and SRS-22 Patient Questionnaire just before every other visit to the orthopedic surgeon, thus 4 times in total. The EuroQol scores can be translated into utilities with values from the Dutch general population. The parents of the patients are requested to fill out the CHQ-PF50, EuroQol and SRS-22 at the same time that their child fills out her/his questionnaires. Patients and parents will receive the questionnaires and a return envelope about two weeks before every other visit to the orthopedic surgeon; thus they can fill out the questionnaires before they know the results of the X-ray (i.e., before knowing whether or not the curvature has progressed).

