IS patients are usually advised to wear the brace for 18–23 hours every day as long as the patient is growing, which often implies wearing the brace during many years in adolescence. Hence, the risk of non-compliance is present. Lack of compliance in this group would lead to an underestimation of the treatment effect, if present, and would reduce the power of the trial. Compliance will be measured by three different means. The orthopedic surgeon will ask the patients and their parents how many hours a day the patients wear the brace. Because the patient has to return every 4 months for a check-up, the brace will be checked for signs of wear and tear typical for an intensively-used brace. Besides this, patients of the intervention group will receive a short questionnaire in which compliance, attitudes, social influences and barriers to wearing the brace will be measured at every other visit to the orthopedic surgeon.

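### Brace compliance, which arises after randomisation and has no counterpart in unbraced controls, is listed with baseline factors as a stratifier of the treatment effect, so that comparison is not randomised and can mislead

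*Protocol article*

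**What the plan says.** The Statistical methods section makes intention to treat the basis of the group comparison and then adds: "Stratified analysis will be done to evaluate whether curve type, brace compliance, Cobb angle at inclusion and Risser sign at inclusion influence the effectiveness". The four factors are treated alike, and nothing marks compliance as different in kind.

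Other sections of the protocol article show that it is different:

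- **Participants** lists the data taken at entry: "At inclusion of the study, data on calendar age, gender, height, maturation characteristics (Risser sign, menarche), size and location of the curvature will be recorded". Compliance is not among them.
- **Follow-up** sets the recurring measurements, beginning "Every four months the orthopedic surgeons will repeat the measurements of size and location of the abnormal curvature, physical height, maturation characteristics". Brace compliance appears later in that same list.
- **Outcomes** makes it an endpoint: "The secondary outcomes of this study concern health-related quality of life (HRQoL) and compliance to brace treatment".
- **Outcomes** also describes three ways of measuring it: reported hours ("The orthopedic surgeon will ask the patients and their parents how many hours a day the patients wear the brace"), inspection of the brace for signs of use, and a questionnaire ("patients of the intervention group will receive a short questionnaire in which compliance, attitudes, social influences and barriers to wearing the brace will be measured").
- **Control group** states: "Patients in the control group will initially not be braced during the two study years, unless their curvature shows more than 10 degrees progression".

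**The concern.** A stratified analysis of a treatment effect keeps the benefit of randomisation only if each stratum is defined by something fixed before allocation and observable in both arms. The three inclusion characteristics meet that condition. Compliance does not. It is behaviour under one of the two treatments, and a control who is never braced has no level of it. A control who is braced has one only after more than 10 degrees of progression, so that value is a consequence of the outcome.

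Two contrasts remain possible: a self-selected part of the brace arm against all controls, or more against less compliant patients within the brace arm. Neither is protected by randomisation. If children who wear the brace more would have had a different course anyway, that difference is read as an effect of the brace, or as a variation in its effect.

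The Outcomes section says that poor compliance would cause the treatment effect to be underestimated. A reader given a neutral overall result and a favourable result in good compliers could easily take the second as the truer answer. The Discussion expects the trial to inform both bracing and the screening programme.

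**Working it through.** **Step 1: can compliance strata contain both arms?** Set the sections side by side. The measures are hours of brace wear, wear of the brace itself, and a questionnaire sent to the intervention group only (Outcomes). Controls start without a brace and may get one only after progression beyond the threshold (Control group). The Follow-up section applies one monitoring protocol to both groups and includes compliance in it, but an unbraced child has nothing to record. So no stratum can be formed in which braced and control patients share a compliance level independent of outcome.

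**Step 2: inputs for an illustration.** The plan gives no figure for this analysis, so there is none to reproduce.

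- SD of change: about 4.5 degrees (Sample size).
- Patients per arm: 40 (Sample size).
- Benchmark: 5 degrees less mean progression (Outcomes).
- Correlation r between compliance and the course the curve would have taken without a brace: not in the documents. Assumed absolute values are 0.2, 0.3 and 0.5, with 0 as reference.

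**Step 3: shift from selection alone when the brace has no effect.** With compliance and progression bivariate normal, a selected group's mean shifts by r × SD × E[Z | selected]. E[Z | selected] is 0.798 for the upper half and 1.091 for the upper third. A simulation of 20,000 trials (40 per arm, brace arm split at median compliance, two-sided 5% t tests) gives the rejection rates.

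| Absolute r | Upper half: 4.5 × 0.798 × r | Upper third: 4.5 × 1.091 × r | Simulated shift, upper half | Upper half vs controls, p < 0.05 | Upper vs lower half, p < 0.05 | Intention to treat, p < 0.05 |
|---|---|---|---|---|---|---|
| 0 | 0 | 0 | 0.0 | 4.9% | 4.8% | 4.8% |
| 0.2 | 0.72 | 0.98 | 0.70 | 8.7% | 16.5% | 5.1% |
| 0.3 | 1.08 | 1.47 | 1.05 | 13.6% | 32.2% | 5.1% |
| 0.5 | 1.80 | 2.45 | 1.76 | 30.6% | 75.4% | 5.1% |

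The simulation took better-prognosis patients as the better compliers, so the shift appears as benefit in the more compliant half and equal harm in the less compliant half. With the opposite sign, the same figures hold by symmetry with benefit and harm exchanged.

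**Step 4: a real and uniform effect.** With a true effect of 5 degrees in everyone and r = 0.3 in that same direction, the two halves would show about 5 + 1.08 = 6.1 and 5 − 1.08 = 3.9 degrees (simulated: 6.06 and 3.95). The effect would appear to depend on compliance when it does not.

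**Step 5: against the 5-degree benchmark.** Take the largest assumed case, r = 0.5, upper half of 20 against 40 controls, with no brace effect. The variance in the selected half is 4.5² × (1 − 0.25 × 0.798²) = 20.25 × 0.841 = 17.0. The standard error is √(17.0/20 + 20.25/40) = √1.356 = 1.16. An observed benefit of 5 degrees or more then lies (5 − 1.80)/1.16 = 2.8 standard errors out, a probability of about 0.3%.

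**Step 6: sensitivity to the SD.** The shifts are proportional to it. A uniform spread over the wider range in the Sample size section, −2 to 17 degrees, has SD 19/√12 = 5.48. The upper-half shift is then 5.48 × 0.798 × 0.2 = 0.9 to 5.48 × 0.798 × 0.5 = 2.2 degrees.

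**The case against.** The strongest reply is that this is a secondary, exploratory analysis. The group comparison is by intention to treat, and no success rule is attached to compliance. That stands, and it limits the weight of the point.

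Further replies also have force:

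- **A reader might infer that the analysis is bound to mislead.** The documents do not support that. At r = 0 there is no bias, and no section says that compliance depends on maturity, curve size or the course of the curve. The nearest statement is a planned check: "Using logistic regression we will also evaluate whether brace compliance depends on gender and age". A link is plausible, since patients and surgeons are unblinded and there is an X-ray every four months, but its size and sign are unknown. If children with worsening curves wear the brace more, the bias hides benefit.
- **A reader might infer that an inert brace could meet the trial's own criterion in good compliers.** On the assumptions above, this is very unlikely (Step 5). The risk is to nominal significance and to the apparent pattern across strata.
- **The text does not say which contrast is meant.** A comparison within the brace arm is a fair reading, given that the questionnaire goes only to that arm. That contrast is also observational, so the reading changes the remedy to a label and baseline adjustment but does not remove the problem.
- **A reader might also fault the plan for naming no test of heterogeneity across the baseline strata.** A condensed article may leave that to the full protocol or the analysis plan, so it forms no part of this point.

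None of this makes compliance a baseline factor or supplies controls with a value for it.

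**Conclusion.** The point holds as a defect in a stated secondary analysis. Compliance is placed among baseline effect modifiers although, by the protocol article's own account, it is recorded after randomisation, is an outcome, and is absent in unbraced controls. No randomised comparison within compliance strata can be formed.

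The possible distortion is moderate: about 0.7 to 1.8 degrees in the more compliant half, or 1.0 to 2.5 degrees in the most compliant third, in either direction. A nominal 5% test against controls would reject in roughly 9% to 31% of trials of an inert brace, counting both directions. These figures rest on an assumed absolute correlation of 0.2 to 0.5, normality, the stated SD of 4.5 degrees and 40 patients per arm. They illustrate the risk and do not estimate it. The intention-to-treat result is untouched.

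**What to change.** 1. Restrict the stratified analysis of effect modification to curve type, Cobb angle at inclusion and Risser sign at inclusion.
2. Report any relation between compliance and progression within the brace arm only, labelled observational and adjusted for baseline factors.
3. If an effect under adherence is wanted, estimate a complier-average effect with allocation as instrument. State the definition of exposure and the assumptions, in particular that allocation affects progression only through brace wear.

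The cost is a change of analysis wording, since the compliance data are already to be collected. There are three downsides. The instrumental-variable interval is wider than the intention-to-treat interval. Exposure rests largely on hours reported by patients and parents, and misreporting distorts any per-hour estimate. The Statistical methods section fixes a control's outcome at the moment bracing starts, so the analysis must say how outcome and exposure are matched in time for those patients. The complier-average effect also answers a different question from whether the effect varies with compliance, and the report should say so.
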